#### Screening for eligibility

Infants at high-risk of NDI will be identified from (1) neonatal admission registers and neonatal follow-up services, (2) local paediatric outpatient services and (3) attendance for early child health services following community sensitisation. Sensitisation will include public health announcements on local radio raising awareness of the research and appropriate child development more generally. Caregivers of high-risk infants (survivors of neonatal encephalopathy, prematurity, neonatal septicaemias/meningitis and severe jaundice) will be contacted by phone and invited to attend an appointment when the child is 6–11 completed months old. After informed written consent, they will be screened for NDI by trained study staff using the Malawi Developmental Assessment Tool (MDAT).^12^ If two or more items in any MDAT domain are not achieved, the child will be referred for comprehensive neurodevelopmental assessment. If the child fails one item in two or more domains, they will be invited back for an assessment in 1 month. If the child’s MDAT scores are age appropriate across all domains, advice will be given on play and stimulation, communication, nutrition and immunisations and the child discharged.

Caregivers of infants screening positive on MDAT will be invited to an appointment for written informed consent, and if provided, comprehensive neurodevelopmental assessment by study staff using the Griffiths Mental Developmental Scales (GMDS)^13^ and the Hammersmith Infant Neurological Examination (HINE).^14^ An overall developmental quotient will be derived, from the GMDS subscales assessing locomotor, personal–social, hearing/language, eye-hand coordination and performance skills.^13^ Neuromotor impairment will be further assessed according to the HINE, a standardised paediatric neurological examination and classified by type. We have used both these tests extensively in previous studies in Uganda and found them easy to administer in this setting and at this age.^15^ The assessments will be conducted in the local language using the standard manual material to ensure internal consistency in the assessments technique. Inclusion and exclusion criteria are outlined in box 1.

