Box 1Eligibility for inclusion in the randomised controlled trialInclusion criteriaInfant aged 6–11 completed monthsModerate–severe neurodevelopmental impairment (NDI) defined as a Griffiths Mental Developmental Scales (GMDS) Developmental Quotient <70 and/or Hammersmith Infant Neurological Examination (HINE) score <60 (Romeo, 2013)Informed written consent by caregiverExclusion criteriaInfants aged 12 months of age or olderInfants screening positive for NDI (using Malawi Developmental Assessment Tool) but not meeting the criteria for moderate–severe NDI on GMDC and HINE assessmentConditions requiring prolonged inpatient treatmentParents unwilling or unable to attend the full programmeMain residence outside Nakaseke or Luwero district, and >20 km from Mulago HospitalAccompanying caregiver not speaking or understanding Luganda or English

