### Baseline characteristics

Infant and caregiver demographic information will be recorded at baseline, including date of birth, age, sex, birth order, parity, antepartum, intrapartum and postpartum history, family and medical history, developmental history, mother’s education and occupation, family details including family size, and ages, household incomes, household SES and residence. All outcome measures will also be measured at baseline enabling preintervention and postintervention comparisons.

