### Outcomes

Participants in both arms will be assessed by study staff masked to trial allocation at two time points; at age 12–17 months (which corresponds to completion of the EIP in the intervention arm, 6 months after recruitment) and again at age 18–23 months (12 months after recruitment). (figure 1). Caregivers will be phoned a week before the follow-up assessments to arrange a time for interview. Assessments will be primarily conducted in the study-site clinics. Where caregivers cannot be contacted by phone or are unable to attend the clinic, a community visit will be arranged, and assessments completed at home. Outcome assessments will be conducted by Mulago assessors for children recruited at Kiwoko, and vice versa to ensure assessors are blind to allocation arm. Two assessors will independently assess a small proportion of the children and inter-rater reliability will be calculated.

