#### Other outcomes of interest

*Child motor functioning* as assessed by the mobility score of the Paediatric Evaluation Disability Inventory (PEDI).^18^ The PEDI is a standardised test designed to identify and describe functional impairment and monitor progress. Normative scaled scores are obtained for children≥6 months to provide age-related expectations of ability.
*Child cognitive function* as assessed by the GMDS.^13^

*Child growth, health and well-being* assessed using weight, height and head circumference measured according to standardised protocol. Occipitofrontal head circumference (paper tape measure), weight (SECA336 electronic scales, Hamburg, Germany) and height will be taken by study staff using standardised procedures. Haemoglobin will be determined on a finger prick sample using HemoCue Hb 201 (HemoCue AB, Angelholm, Sweden). A structured maternal interview in Luganda will report on caregivers concerns regarding health, growth and development of their child and episodes of illness including seizures and other neurological problems, feeding difficulties, chest infections and treatment for malnutrition.
*Caregiver psychological distress* assessed using the Self-Referral Questionnaire (SRQ) and the Parenting Stress Index (PSI).^19^ The SRQ consists of 20 items each scored 0 (symptom absent) or 1 (symptom present) giving a total out of 20. The PSI is a 120-item inventory measuring the magnitude of caregiver stress attributable to parent–child relationship (Total Stress Scale), and situational/demographics factors outside the parent–child relationship (Life Stress Scale). These tools will be translated into Luganda.
*Caregiver–child attachment* assessed using the Maternal Infant Responsiveness Instrument; a 22-item scale designed to measure the parent’s feelings about their infant and an appraisal of the infant’s responses.^20^

*Quality of the home environment* assessed using the Infant Toddler-Home Observation for the Measurement of the Environment. This comprises 45 items, based on observation and/or interview, assessing the physical environment of the home and the child’s interaction within it.^21^

*Cost of illness and protective effectiveness* will be assessed (separate protocol, [name] *et al*).

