### Statistical analysis

The first primary outcome, feasibility of participant recruitment and randomisation, will be assessed by the total number recruited and randomised to each arm. Recruitment and randomisation feasibility will be demonstrated if the target sample size of 126 is achieved. Data on participants screened, eligible and randomised will be displayed in a Consolidated Standards of Reporting Trials flow chart. Descriptive statistics (frequencies, means, medians, SD and IQRs) will be used to describe the sample at baseline, by trial arm.

The second primary outcome, acceptability, will be assessed quantitatively by (1) calculating the protocol violation rate and (2) summarising the number of programme sessions attended between baseline and programme completion for those in the intervention arm. Protocol violation rate will be calculated as the number of participants for whom one or more protocol violations occur divided by the total number of participants, and will be presented both overall, and by trial arm. For participants in the EIP trial arm, the overall number of modules attended by each participant will be tabulated. Acceptability on the basis of number of programme sessions will be defined as attendance of at least six modules.

For the third primary outcome and secondary outcomes, analyses will compare outcomes between intervention and control arms at the end of the programme, when the participants will be aged 12–17 months, and again 6 months later. Analysis will be on an intention-to-treat basis and missing data will not be imputed. Data for each outcome measure will be summarised by trial arm, using proportions for binary outcomes and means or medians for quantitative outcomes, depending on normality of the distribution. Differences in means/proportions between trial arms together with 95% CIs will be calculated. We do not plan any formal statistical tests due to the preliminary nature of the trial; instead CIs will provide a possible range of effect sizes. Regression models (linear regression for continuous outcomes, logistic regression for binary outcomes) will be used to adjust comparisons for baseline measures of the outcomes, which were collected at enrolment into the trial, in order to improve precision of effectiveness estimates. For skewed continuous outcomes, data will be normalised before analysis using suitable transformations or quantile regression will be considered. No subgroup analyses are planned.

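### Adding the baseline HINE score to the PEDI mobility model could narrow its interval at almost no cost; the stated covariate rule leaves it out

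*Protocol article*

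**What the plan says.** Under Statistical analysis, the protocol article says regression models will be used to "adjust comparisons for baseline measures of the outcomes, which were collected at enrolment into the trial". The stated purpose is "in order to improve precision of effectiveness estimates". No further covariate is named. No formal tests are planned, and confidence intervals are to convey the range of possible effects.

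Under Baseline characteristics: "All outcome measures will also be measured at baseline enabling preintervention and postintervention comparisons". Child motor functioning is listed under Other outcomes of interest and is measured by the mobility score of the PEDI, so the rule makes baseline PEDI mobility its covariate. On that instrument the article adds: "Normative scaled scores are obtained for children≥6 months to provide age-related expectations of ability". Infants enter at 6–11 completed months. Follow-up is at 12–17 and 18–23 months of age.

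The HINE belongs to the assessment that decides eligibility (Screening for eligibility): "Neuromotor impairment will be further assessed according to the HINE, a standardised paediatric neurological examination and classified by type". Box 1 defines moderate–severe impairment by a Griffiths "Developmental Quotient <70 and/or Hammersmith Infant Neurological Examination (HINE) score <60". HINE is listed neither among the primary outcomes nor among the other outcomes, so a rule built on baseline values of outcomes does not bring it into any model.

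**The concern.** Adjusting for an outcome's own baseline helps only as far as that baseline predicts the follow-up value. PEDI mobility is first measured here close to the age at which its norms begin, in infants chosen because they are impaired. It is reasonable to expect many low scores with little spread, and hence a modest correlation with mobility 6 and 12 months later. The same infants will already have a HINE score, which grades neuromotor impairment directly.

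At stake is the width of one interval. That matters somewhat in this trial: with no tests planned, the interval is what the motor analysis delivers, and the article says the data will inform a larger trial on child and family outcomes. Randomisation is stratified by recruitment centre alone, so the arms may differ by chance in neuromotor severity. A severity covariate would account for that.

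**Working it through.** **Inputs from the protocol article.** 126 infants, 63 per arm, 20% dropout, 90% power, 5% significance (two-sided assumed), PedsQL mean 65 with SD 20, and a 20% relative difference, which is 13 points (Sample size).

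**The plan's own figure.** n per arm = 2 × (1.96 + 1.2816)² × 20² / 13² = 49.7, rounded up to 50. Dividing by 0.80 gives 62.5, rounded up to 63 per arm, or 126 in total. The stated size reproduces. It rests on PedsQL without baseline adjustment, so this point does not touch it. No precision figure is stated for the motor outcome.

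**Inputs that must be assumed.** The article gives no PEDI distribution and no correlations. Write:
- r1 = correlation of baseline PEDI with follow-up PEDI
- r2 = correlation of baseline HINE with follow-up PEDI
- r12 = correlation of baseline PEDI with baseline HINE

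**Formulas.** With 50 completers per arm, the unadjusted 95% half-width is 1.96 × √(2/50) = 0.392 SD. Adjustment multiplies this by √(1 − R²). For PEDI alone, R² = r1². For both covariates, R² = (r1² + r2² − 2·r1·r2·r12) / (1 − r12²). The equivalent number of completers per arm is 50 divided by the ratio of the two residual variances.

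**Baseline PEDI weak (r1 = 0.2, r12 = 0.3).** PEDI alone: 0.392 × √0.96 = 0.384 SD.

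| r2 | R² with both | Half-width | Variance ratio to PEDI alone | Equivalent completers per arm |
|---|---|---|---|---|
| 0.3 | (0.04 + 0.09 − 0.036)/0.91 = 0.103 | 0.371 SD | 0.93 | about 54 |
| 0.5 | (0.04 + 0.25 − 0.060)/0.91 = 0.253 | 0.339 SD | 0.78 | about 64 |
| 0.7 | (0.04 + 0.49 − 0.084)/0.91 = 0.490 | 0.280 SD | 0.53 | about 94 |

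Against PEDI alone, the interval narrows by about 3%, 12% and 27%.

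**Baseline PEDI informative, HINE weaker and overlapping (r1 = 0.5, r2 = 0.3, r12 = 0.5).** PEDI alone: 0.392 × √0.75 = 0.339 SD. Both: R² = (0.25 + 0.09 − 0.15)/0.75 = 0.253, half-width 0.339 SD, variance ratio 0.996. The gain is nil for practical purposes.

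**Cost of a useless covariate.** With about 100 completers, residual degrees of freedom fall from 97 to 96. The interval widens by a factor of about √(97/96) = 1.005, or roughly 0.5%.

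**The case against.** The strongest reply is that nothing here is wrong. Adjusting each outcome for its own baseline is standard and valid, and the baselines are to be collected. The text names no other covariate but does not exclude one, and an analysis plan that is not shown may already include HINE. All of this stands, and it limits the point to a suggestion.

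A reader might go further and infer that baseline PEDI must sit on its floor and that HINE is the informative baseline. The documents do not support that. The norms cover the whole entry range, and only the youngest infants are at their lower limit. No floor proportion or correlation is reported. Because the criteria are joined by and/or, an infant can enter on the developmental quotient alone, so neuromotor impairment need not be present in all. A HINE score below 60 is itself a route to entry, so selection may restrict the HINE range as well as the PEDI range.

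A reader might also infer that HINE serves eligibility alone. It also classifies impairment by type, and it appears in the legend of Figure 1, which is not shown. What can be said is that the stated covariate rule does not use it.

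Finally, the outcome is not primary, the trial is a pilot, and the interval already allows for chance imbalance between arms. These facts reduce the importance of the point. They do not remove it, because precision is the stated reason for adjusting and the covariate is already collected.

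**Conclusion.** The point holds as a minor improvement. The covariate rule, read as written, gives the PEDI mobility model baseline PEDI and leaves out a neuromotor severity measure that should exist for every randomised infant. It would be wrong to conclude that the motor comparison is biased or that the plan contradicts itself: randomisation protects the estimate with or without HINE. Feasibility, acceptability, PedsQL and the sample size are unaffected.

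The benefit runs from nothing to substantial, and the documents cannot say where in that range the trial will fall. Every correlation used is an assumption, and a weak baseline PEDI is an expectation only. The case rests on asymmetry: a loss of about 0.5% of interval width if HINE adds nothing, against a narrowing of about 3% to 27% in the scenarios where baseline PEDI is weak.

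**What to change.** First check whether the analysis plan already includes HINE. If not, add one sentence to Statistical analysis: the PEDI mobility models at both follow-up times will include the baseline HINE score as an additional covariate, alongside baseline PEDI mobility.

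This costs one degree of freedom and needs no new data. Since HINE is scored before randomisation, it should not lose cases under the rule that missing data are not imputed. Naming it in advance also avoids a choice of covariate made after the data are seen.

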### Trial management, data monitoring and reporting of adverse events

The Trial Steering Committee (TSC)^22^ will oversee progress of the study towards its objectives, review relevant information from other sources (eg, other related trials) and receive reports from the Data and Safety Monitoring Board (DSMB). All adverse events, whether related to the intervention or not, will be noted and reported. A Data Monitoring and Safety Committee has been established independent of the investigators and the TSC but reporting to the TSC and the sponsor. The DSMB includes an expert on global child heath, a senior statistician and a senior academic working in newborn and early child health research in Uganda, independent of the investigators. The DSMB will have access to all data on request. Resulting from the initial meeting of the DSMB on 28 June 2017, no formal stopping rules will be applied.

Children with NDI and particularly those with seizure disorders and difficulties with swallowing are at increased mortality risk. All adverse events, whether related to the intervention or not, will be investigated and reported according to the UVRI Research Ethics Committee (REC) in accordance with good clinical practice requirements. All deaths, hospitalisations and other serious adverse effects will be reported to the relevant ethics committee irrespective of whether the death or event is related to disease progression or not. Trial data monitoring will be conducted by an internal independent monitor at initiation, 6 months into data collection, again after 1 year and end of data collection.

## Participant and public involvement

The intervention, study design and conduct were developed directly from the engagement of caregivers and programme facilitators (‘expert parents’) with a parent representative on the TSC. The priorities and experiences of caregivers identified during facilitated group discussions at a key-stakeholders meeting (June 2017) contributed to the development of our research question and outcome measures. Plans to communicate findings to participants and the wider community will involve caregivers, through formal discussions with the TSC.

## Ethics and Dissemination

### Ethics

The protocol has been approved by the Research and Ethics committee of the UVRI, Mulago Hospital and Kiwoko Hospitals, the Uganda National Council for Science and Technology, the Uganda President’s Office, and the ethics committee of the LSHTM. Information sheets will be available in English and Luganda, the main local language. Parents will be provided with an oral and written explanation of the study by Ugandan study staff to ensure that information is accessible to those with lower levels of literacy. Witnessed consent using a thumb print will be available to parents/guardians who are non-literate. Reimbursement for the cost of transport will be provided to caregivers on attendance at the screening and recruitment visits.

All recruited children will receive SC at the study sites. This will include referral to local services for seizure management and physiotherapy where available. To date, the benefits of the proposed EIP have not been proven and may have a negative effect if children are incorrectly classified as having NDI and placed in the programme. Children and their caregivers in the control arm will receive delayed entry into the programme for older children (‘Getting to Know Cerebral Palsy’) at 18–23 months at the time of their final study assessments.

### Dissemination

Our programme has strong links with partnership organisations working in Maternal and Child Health programming including Adara Development, Kiwoko Hospital, Nakaseke District Health Office and other collaborating institutions. Research findings will be disseminated to the Ministry of Health, to inform local and national health policies. Regional-level stakeholders, including the Nakaseke District Health Office and heads of regional health and social services, will be engaged to support staff recruitment, contributing to the sustainability of the innovation at local and district levels. Meetings for key stakeholders, including local Non-Governmental Organisations working in child disability will be held twice during the project period to promote buy-in, facilitate fast-cycle learning, disseminate study findings and ultimately promote sustainability of the programme. Global learning will be facilitated through our existing online community of practice spanning 70 countries and >300 members. Communications support staff at MRC/UVRI, LSHTM and Adara Development will facilitate dissemination of information through appropriate media outlets, the web and social media.

Study findings will be published through Open Access peer-reviewed journals, presentations at local, national and international conferences and to the local community through community meetings. Written reports will be submitted to UVRI REC and reported to the trial registry. Data will be made available on request.
